**Methods:**

One hundred T2D patients from general practices in the Netherlands with a BMI ≥ 27 kg/m^2^, treated with lifestyle advice only or lifestyle advice plus metformin, will be randomised to receive the FMD plus usual care or usual care only. Primary outcomes are HbA1c and T2D medication dosage. Secondary outcomes are anthropometrics, blood pressure, plasma lipid profiles, quality of life, treatment satisfaction, metabolomics, microbiome composition, MRI data including cardiac function, fat distribution and ectopic fat storage, cost-effectiveness, and feasibility in clinical practice.

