### Power calculation

The number of participants that will be included in the study is limited to 100 (50 in each group). We computed expected effect sizes with a sample size of 100. As all participants will be asked to come in for T8, we work with a limited loss to follow-up of 10% [8], thus basing the calculations on 90 participants (45 in each group).

We computed the effect size that can be detected with 80% power for the binary endpoint, which is equal to one if either a lower dose of antidiabetic medication is used at the end of the study compared to the start, if HbA1c is at least 5 mmol/mol lower at the end compared to study start, or both.

The expected percentage of participants in the control group who will reach this endpoint is between 4 and 6% [8, 31]. For this power calculation, we assumed a percentage of 5% of participants in the control group who will reach the combined endpoint. With a significance level of 5 and 80% power, using a two-sided binomial test with 45 participants in each group, an absolute difference in percentages of 21% (i.e. 5% in the control group and 26% in the treatment group) can be detected.

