### Primary and secondary outcomes

Primary and secondary outcomes will be summarized using mean and standard deviation, or in case of an asymmetric distribution, by using median and interquartile range. HbA1c and antidiabetic medication dosage will be compared between the two groups, using t-tests for independent samples, or, if the assumption of normality is violated, with a Mann-Whitney U test. The values at 12 months will be used for these tests.

To compare the total successful outcomes, the primary endpoints HbA1c and antidiabetic medication dosage will be combined. A successful outcome will be defined as any reduction in the antidiabetic medication dosage and/or a decrease of HbA1c of 5 mmol/mol or more. This will be compared between the two groups as described above. To correct for multiple testing, the procedure of Benjamini-Hochberg will be used.

To detect a difference in the profiles of the outcomes that are measured repeatedly during the course of the study, a mixed model will be used. This model can be used if there is missing data, and if participants have their visits at different time points. The interaction between time and treatment arm will be included. Besides a random slope per participant, a random intercept and the inclusion of splines will be considered. In case complete observations are available for at least 80% of the participants, and if the pattern of missing observations is deemed noninformative, the mixed model will be compared to a generalized least squares model with unstructured, compound symmetry, or AR (1) covariance structures. The choice between the options will be made using the AIC criterion.

As multiple primary endpoints are measured repeatedly, multiple mixed models will be fit. For each of the models, the outcome of the global F or LR test (where appropriate) will be reported, and significance evaluated using the procedure of Benjamini-Hochberg.

The secondary outcome ‘feasibility in practice’, measured as the percentage of compliant participants, will not be tested, as there is no reference value for comparison.

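### The stated 80% power assumes an unadjusted 5% test of the 12-month composite, but the analysis section puts that test under a Benjamini-Hochberg correction, so 80% is not assured

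*Protocol article*

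**What the plan says.** **Power.** The Power calculation section of the protocol article concerns one endpoint: "We computed the effect size that can be detected with 80% power for the binary endpoint". It describes the test as follows: "With a significance level of 5 and 80% power, using a two-sided binomial test with 45 participants in each group". The result is "an absolute difference in percentages of 21% (i.e. 5% in the control group and 26% in the treatment group) can be detected". Enrolment is capped at 100, and 10% loss leaves 90 evaluable. No allowance for multiple testing is mentioned.

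**Analysis.** The Primary and secondary outcomes subsection of the statistical analysis first compares HbA1c and dosage between arms at 12 months. It then combines them into the success endpoint, compares that too, and closes the paragraph with "To correct for multiple testing, the procedure of Benjamini-Hochberg will be used". Two paragraphs later it adds "As multiple primary endpoints are measured repeatedly, multiple mixed models will be fit" and gives those models a Benjamini-Hochberg sentence of their own.

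**Status of the endpoints.** The abstract says "Primary outcomes are HbA1c and T2D medication dosage". The Primary study objective speaks of combined primary outcomes. The Primary outcome section names the two endpoints and then merges them into one success outcome at 12 months.

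**The concern.** Under Benjamini-Hochberg, the level at which the composite is judged depends on the p-values of the other tests in the family. With three tests it is 0.0167 if the composite is the only small p-value, 0.0333 if one other joins it, and 0.05 only if all three are at or below 0.05. A power figure computed at a flat 5% therefore describes the most favourable case.

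The protocol gives reasons why a companion test could be weak. Under Usual care, GPs in both arms may adapt medication towards an HbA1c target of 53 mmol/mol, which tends to pull 12-month HbA1c values together. The inclusion criteria admit people on lifestyle advice alone, who start with no antidiabetic dose to reduce, and this dilutes the dosage comparison. The composite could move while one component test stays non-significant.

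At stake is whether a trial that cannot enrol beyond 100 has the power it reports. It is also unclear whether a primary claim rests on the composite or on any of the tests that survives the correction.

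**Working it through.** **Inputs from the Power calculation section:** p1 = 0.05, p2 = 0.26, n = 45 per arm (100 × 0.9 = 90), two-sided 5%, power 80%.

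**1. Reproduce the stated power.** Pooled normal approximation:

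power = Φ{[(p2 − p1) − z·SE0] / SE1}

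- Mean rate = (0.05 + 0.26)/2 = 0.155
- SE0 = √(2 × 0.155 × 0.845 / 45) = 0.0763
- SE1 = √[(0.05 × 0.95 + 0.26 × 0.74)/45] = 0.0730
- With z = 1.960: (0.21 − 0.1495)/0.0730 = 0.828, so power = **79.6%**

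The stated 80% is reproduced, and it belongs to an unadjusted 5% test.

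**2. The same formula at the three Benjamini-Hochberg steps (three tests).**

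| Level | z | Power for 5% vs 26% |
|---|---|---|
| 0.05 | 1.960 | 79.6% |
| 0.0333 | 2.128 | 74.3% |
| 0.0167 | 2.394 | 64.6% |

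**3. Detectable rate and sample size at 0.0167.** Solving the formula for p2 at 80% power gives 30.7%, about 31%, against 26.1% at 5%. To keep 5% versus 26%:

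n = [2.394 × √0.26195 + 0.842 × √0.2399]² / 0.21² = (1.225 + 0.412)²/0.0441 = 60.8, so 61 evaluable per arm

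That is 122/0.9 = 135.6, or 136 randomised, against a cap of 100.

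**4. Full procedure, simulated.** Three normal test statistics with common correlation 0 to 0.7, Benjamini-Hochberg at 5%, at least 300,000 draws per setting. The correlations and the strengths of the other two effects are assumptions, because the protocol gives neither.

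| HbA1c and dosage tests | Composite power |
|---|---|
| No effect on either | about 66% |
| 30% power each | 67 to 70% |
| 50% power each | 69 to 73% |
| Powered like the composite | 76 to 78% |
| Certain to reject | 80% |

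**5. Familywise error, three tests.** With all three hypotheses null, the simulated error is 4.2 to 5.0%. With one endpoint certain to reject and two independent true nulls, a false rejection occurs if either null p-value is at or below 0.0333, or if both lie between 0.0333 and 0.05:

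1 − (1 − 0.0333)² + 0.0167² = 0.0656 + 0.0003 = **6.6%**

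With correlation the simulated figure is lower, 5.7 to 6.5%. With two real effects and one true null left, it is about 5%.

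**The case against.** **The power loss is conditional.** The 66% figure needs no effect on HbA1c or dosage while success, which is built from those two, rises from 5% to 26%. That is extreme. If both components move as strongly as the composite, the loss is only 2 to 4 points. The choice of test for a binary endpoint matters more than that: at 5%, exact power for the same rates is 74.6% with Fisher's test and 84.1% with the uncorrected chi-square test. This objection stands, and it is why the size is given as a range. It does not remove the mismatch: no scenario run gave more than the uncorrected figure, and the stated power was recovered only when both other tests were certain to reject.

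**The composite is already the main endpoint.** The objective, the Primary outcome section and the power calculation all point to it. A reader might infer from the abstract and the analysis section that nothing indicates the decisive result; that is too strong. What remains is that the analysis section does not exempt the composite from the correction and still refers to several primary endpoints.

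**Family membership is usually settled in the SAP.** True, and the absence of a list is not held against the article. But the article itself states both the power level and the correction, and the two do not match.

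**Two stronger readings are not supported.** A reader might infer that familywise error exceeds 5% whenever this plan is used. It does not: if the diet has no effect, Benjamini-Hochberg holds it at about 5% or below. Excess needs one real effect alongside two true nulls. A real effect on a component will usually move the composite too, leaving a single null and error near 5%. The protocol also never claims strong familywise control. A reader might also count the mixed models in the same family and quote five-test figures (power of 58 to 59% with all other tests null, familywise error up to 8.7%). Those models have a separate Benjamini-Hochberg sentence and are not said to be pooled with the 12-month tests, so such figures rest on an assumption.

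**Conclusion.** The mismatch is real. The 80% applies to the composite tested alone at 5%, whereas the analysis section most naturally places it in a Benjamini-Hochberg family with 12-month HbA1c and dosage. In that family its power lies between about 66% and 80%, with 69 to 78% covering the intermediate cases of 50% power per component up to components as strong as the composite. The three-test family is a reading of the text; the correlations and the other effect sizes are assumed. Benjamini-Hochberg controls the false discovery rate and gives no strong familywise control, but the possible excess with three tests is modest (up to about 6.6%) and needs an unusual pattern, so it is a secondary point. Severity: should fix.

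**What to change.** In the Primary and secondary outcomes analysis text, name the 12-month composite as the single confirmatory primary test at two-sided 5%, outside the Benjamini-Hochberg procedure. Treat 12-month HbA1c, dosage and the mixed models as secondary or supportive, and keep Benjamini-Hochberg there. Align the abstract, the Primary study objective and the Primary outcome section with this, before outcome data are analysed.

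If the composite is to stay inside the correction, restate the power at the adjusted level instead: with 45 per arm and three tests, 64.6% for 5% versus 26% at the strictest step, or a detectable rate of about 31%.

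The first option costs only wording and makes the stated 80% hold with the planned 100 participants. Its downside is that HbA1c or dosage alone could no longer support a primary claim.

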### Baseline data

Baseline data from the two groups will be compared on the following baseline values: age, gender, BMI and metabolic parameters. The values will be summarized using mean and standard deviation, or in case of an asymmetric distribution, by using median and interquartile range.

Hypothesis tests will be carried out using t-tests for independent samples, or, if the assumption of normality is violated, with a Mann-Whitney test. Multiple testing will be corrected for by using the Benjamini-Hochberg procedure. If the groups are found to be imbalanced on one or more covariates, then the following analyses will be adjusted for those covariates. Furthermore, the following analyses will be adjusted for gender and for weight < 100 kg or > 100 kg, since randomization is stratified for these values.

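### On its ordinary reading, the repeated-measures model estimates a separate baseline mean for each randomised arm; this is valid but costs some precision, about 1 to 15% in standard error over plausible correlations

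*Protocol article*

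**What the plan says.** Under Primary and secondary outcomes, the stated aim of the repeated-measures analysis is "To detect a difference in the profiles of the outcomes that are measured repeatedly". The only fixed-effect structure given is "The interaction between time and treatment arm will be included". On the random part: "Besides a random slope per participant, a random intercept and the inclusion of splines will be considered". If enough data are complete and missingness is judged noninformative, the comparator is a "generalized least squares model with unstructured, compound symmetry, or AR (1) covariance structures", with the choice made by AIC. A global F or likelihood-ratio test is reported for each of the models for the primary endpoints.

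Under Baseline data, two adjustment rules apply to later analyses. One is conditional: "If the groups are found to be imbalanced on one or more covariates, then the following analyses will be adjusted for those covariates". The other is fixed: "the following analyses will be adjusted for gender and for weight < 100 kg or > 100 kg".

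Table 2 and the list of secondary outcomes place HbA1c, medication dosage and most secondary outcomes at T0, 6 and 12 months. Anthropometrics and blood pressure are taken at every visit from T0 to T8. HbA1c and dosage are also compared by separate two-sample tests: "The values at 12 months will be used for these tests".

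**The concern.** Both arms are drawn from one randomised population, and T0 precedes the first diet cycle, so the expected T0 means are equal. A model with arm, time and arm-by-time terms nevertheless estimates a T0 difference, and its 12-month effect is then a difference in change from baseline. Setting the T0 means equal uses the design information and gives a smaller standard error for the same data.

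The Baseline data section does not supply the missing constraint. It tests the arms for T0 differences and adjusts only for covariates found imbalanced, plus the two stratification factors. Gender and weight stratum do not stand in for a participant's own baseline HbA1c, lipids or MRI value.

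What is at stake is precision. The Power calculation section limits the sample to 100, with 90 expected at 12 months, so efficient use of baseline data is one of the few ways left to gain information.

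**Working it through.** **The plan's own figure.** The protocol gives no standard error, within-person correlation or power for any mixed model. Its one power statement (5% versus 26%, 45 per arm) concerns the binary endpoint. It reproduces with the pooled normal approximation: mean proportion 0.155; null standard error √(2 × 0.155 × 0.845/45) = 0.0763; alternative standard error √((0.05 × 0.95 + 0.26 × 0.74)/45) = 0.0730; z = (0.21 − 1.96 × 0.0763)/0.0730 = 0.83; power 79.6%. The present point leaves that figure unchanged.

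**Inputs.** 45 per arm (Power calculation). Visit patterns from Table 2: three visits (0, 6, 12 months) or nine (T0 to T8, placed by assumption at 0, 0.25, 1.5, 3.5, 6, 7.5, 9.5, 11.5 and 12 months). All correlations and variance components below are assumptions.

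**Step 1: categorical time, complete data, equal variances.** Let r be the correlation between T0 and 12 months, s² the variance and n the number per arm.

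- Free baseline means: variance = 2(1 − r)s² × 2/n
- Common baseline mean: variance = (1 − r²)s² × 2/n
- Ratio = 2/(1 + r); standard-error ratio = √(2/(1 + r))

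| r (assumed) | Variance ratio | Excess standard error | 90 × variance ratio |
|---|---|---|---|
| 0.5 | 1.333 | 15.5% | 120 |
| 0.7 | 1.176 | 8.5% | 106 |
| 0.8 | 1.111 | 5.4% | 100 |
| 0.9 | 1.053 | 2.6% | 95 |
| 0.95 | 1.026 | 1.3% | 92 |

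The last column is the number of people the free-baseline model would need to match the common-baseline model on 90. Generalized least squares information matrices gave the same ratios for three, five and nine visits under compound symmetry and AR(1).

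**Step 2: linear time.** With nine visits and compound symmetry, the excess is smaller: 8.1% at r = 0.5, 3.8% at 0.7, 2.3% at 0.8 and 1.0% at 0.9.

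**Step 3: random intercept and slope.** With unequal variances, categorical time and complete data, the variance ratio is (V0 + V12 − 2C)/(V12 − C²/V0), where V0 and V12 are the variances at T0 and 12 months and C is their covariance. Assume intercept variance 1, slope standard deviation 0.5 or 0.7 per 12 months, and residual variance 0.1 or 0.2.

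- Independent intercept and slope, slope SD 0.5, residual 0.2: V0 = 1.20, V12 = 1.45, C = 1.00. Ratio = 0.650/0.617 = 1.054; standard error +2.7%.
- Intercept-slope correlation −0.5, slope SD 0.7, residual 0.2: V0 = 1.20, V12 = 0.99, C = 0.65. Ratio = 0.890/0.638 = 1.395; standard error +18%.

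Over the grid (three or nine visits, linear or categorical time):

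| Intercept-slope correlation (assumed) | Excess standard error |
|---|---|
| 0 | 0.1 to 2.7% |
| −0.3 | 5.7 to 9.2% |
| −0.5 | 15 to 19% |

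A larger residual variance (0.25, slope SD 0.5, independent) gives up to 3.6%. Independence makes the variance grow over follow-up; a roughly constant variance requires a negative correlation. For HbA1c a negative correlation is plausible, because the Usual care section has treatment adapted towards a target value, which tends to pull high starters down more.

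**The case against.** **The free baseline is inferred.** The quoted sentence names an interaction and nothing else. A common-baseline model also contains a time-by-arm term, so the sentence fits both, and a journal article may leave the parameterisation to an analysis plan that is not shown. This stands: the point rests on the ordinary reading, not on an explicit statement.

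**The free-baseline model is legitimate.** A reader might infer that a chance T0 imbalance biases the treatment effect through regression to the mean. Over randomisations it does not; the contrast is distorted only conditionally on an imbalance that has occurred. The conditional adjustment rule answers this in part, since metabolic parameters are among the baseline values compared. It acts only when an imbalance is declared, however, and does not recover the precision otherwise.

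**The size is not fixed.** A reader might infer a loss of 5 to 15% on every repeated outcome. The protocol gives no correlation. With categorical time that range needs r of about 0.51 to 0.81, and the random-slope model can give almost no loss. IGF-1 and IGF-BP-1 are measured in the diet group only and have no arm comparison.

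**The planned test is global.** The percentages above describe the 12-month contrast, whereas the protocol reports a global F or likelihood-ratio test. No mixed model is powered, so the sample-size equivalents are illustrative.

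**The constraint has a condition.** Randomisation follows consent and screening, participants are not blinded, and questionnaires are completed at T0. The text does not say whether T0 precedes disclosure of allocation, and the timeline figure is not available here. This stands and is carried into the fix.

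**Conclusion.** The point holds as a modest efficiency recommendation. If arm, time and their interaction are all fitted, freeing the T0 means cannot lower the standard error of the 12-month arm difference and usually raises it. The excess is about 1% (r = 0.95) to 15% (r = 0.5) with categorical time, complete data and equal variances. It runs from near zero to above 15% under a random intercept and slope, according to their assumed correlation.

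The documents do not support reading this as an invalid analysis or as a loss of power for the main comparison. The binary success endpoint and the two-sample tests of HbA1c and dosage at 12 months do not use this model.

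**What to change.** State how baseline enters the repeated-measures models. For outcomes measured repeatedly in both arms, fit T0 as a response with one mean common to both arms: time effects, plus time-by-arm effects after baseline only, with no arm effect at T0. Keep the adjustment for gender and weight stratum. Report the 12-month arm difference with its confidence interval beside the global test. The same fixed effects serve the mixed and the generalized least squares versions.

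The cost is one line in the analysis plan, with no new data. There is a small downside: the constraint assumes that knowledge of allocation has not influenced T0 values. For self-reported T0 measures (quality of life, treatment satisfaction, diet and physical activity), confirm that T0 precedes disclosure of allocation, or keep the free-baseline model for those outcomes.

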### Primary outcome

The primary endpoints of the study are HbA1c and antidiabetic medication dosage. These primary endpoints will be combined to compare the total successful outcomes between the FMD group and the control group after 12 months of follow up. A successful outcome will be defined as any reduction in the antidiabetic medication dosage and/or a decrease of HbA1c of 5 mmol/mol or more. HbA1c and antidiabetic medication dosage will also be recorded after 6 months.

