### Statistical analysis

Data will be analysed on an intention-to-treat basis at the 12-month point. In addition, a per protocol analysis well be carried out. A significance level of 5% will be used.

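### The time shape of the profile model (line or splines) is left to the trial data and then tested at 5% as if fixed; if splines enter the time-by-arm interaction, the three-visit profile test has a type I error of up to about 7%

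*Protocol article*

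**What the plan says.** The article's Statistical analysis section sets the level for all tests: "A significance level of 5% will be used". Under Primary and secondary outcomes it gives the purpose of the longitudinal model, in a sentence that names the method and begins "To detect a difference in the profiles of the outcomes that are measured repeatedly during the course of the study, a mixed model will be". On the mean structure it states "The interaction between time and treatment arm will be included". On what remains open it states "Besides a random slope per participant, a random intercept and the inclusion of splines will be considered". If at least 80% of participants have complete observations and missingness is judged noninformative, "the mixed model will be compared to a generalized least squares model with unstructured, compound symmetry, or AR (1) covariance structures". The paragraph ends "The choice between the options will be made using the AIC criterion".

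The next paragraph applies these models to the primary endpoints, one model for each. For each model "the outcome of the global F or LR test (where appropriate) will be reported, and significance evaluated using the procedure of Benjamini-Hochberg".

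The primary endpoints have few time points. The Primary outcome section sets the main comparison at 12 months and adds that "HbA1c and antidiabetic medication dosage will also be recorded after 6 months". Table 2 schedules HbA1c and medication dosage, after screening, only at T0, T4 and T8.

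**The concern.** A straight-line interaction and a spline interaction are different hypotheses with different degrees of freedom. AIC favours the curved model partly when the chance difference in curvature between the arms is large. That same difference is then part of what the global test assesses. A test that treats the selected shape as if it had been fixed gives p-values that are too small on average.

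At stake is the error rate of inferential tests on primary endpoints. Benjamini-Hochberg takes valid p-values as its input and does not remove the excess. What the test means (a difference in slopes, or any difference in profile) would also depend on the data.

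**Working it through.** **Inputs from the article.** Level 5%. Three planned visits for HbA1c and dosage (T0, T4, T8). Analysed sample 90, that is 45 per arm (Power calculation). Time-by-arm interaction included. Selection by AIC.

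**Assumptions, not in the article.** Normal outcome, complete data, visits at common times, no arm effect, and splines entering the interaction unless stated otherwise.

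**Set-up.** With three visits a spline adds at most one term to the common trend and one to the interaction. Under the null, let A be the squared standardised arm difference in slope, B the arm difference in curvature and C the common curvature. They are independent. A and B are chi-square on 1 df, and so is C if the common trend is linear. AIC charges 2 per extra parameter. The line model is tested by A > 3.84 (1 df) and the curved model by A + B > 5.99 (2 df).

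**Step 1: the stated 5%.** With the shape fixed in advance, both tests run at 5.0%. A finite-sample simulation (90 participants, three visits, 40,000 runs per setting) gives 4.8% to 5.2%.

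**Step 2: AIC adds the common curve and the interaction curve together.** The curved model is picked when B + C > 4.
- Linear common trend: probability of picking it = exp(−2) = 13.5%.
- Line picked: A is independent of the choice, so this contributes (1 − 0.1353) × 0.05 = 0.0432.
- Curve picked: P(B + C > 4 and A + B > 5.99) = 0.0287 by numerical integration, so the test rejects in 0.0287 / 0.1353 = 21% of these trials.
- Total: 0.0432 + 0.0287 = 0.0719, or **7.2%**. The finite-sample simulation gives 7.1%.

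**Step 3: AIC decides only on the interaction curve.** The curved model is picked when B > 2.
- Probability 15.7%.
- Total: (1 − 0.1573) × 0.05 + 0.0329 = 0.0421 + 0.0329 = 0.0750, or **7.5%**. The finite-sample simulation gives 7.2% to 7.6%.

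**Step 4: dependence on what the article leaves unstated.**

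| Situation | Type I error |
|---|---|
| Step 2 rule, common curvature z = 0 | 7.2% |
| Step 2 rule, z = 1 | 6.9% |
| Step 2 rule, z = 2 | 6.1% |
| Step 2 rule, z = 3 | 5.3% |
| Step 2 rule, z = 4 | 5.0% |
| AIC among line, common spline only, and both (linear common trend) | 7.3% |
| Global test also covers the arm main effect (linear common trend) | 6.6% to 6.9% |
| Splines in the common trend only, interaction linear | 5.0% |

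**Step 5: Benjamini-Hochberg.** With two or three independent null endpoints tested this way under a linear common trend, the chance of any rejection is 7.4% to 7.7% instead of 5%.

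**Step 6: covariance selection.** A simulation of 1,600 trials, with AIC also choosing the covariance, gives 7.25% (Monte Carlo error 0.65 points), against 4.75% for a fixed visit-factor model. It assumes an SD of 9 to 10 and correlations of 0.55 to 0.65, which are not in the article. The result does not differ detectably from the 7.2% of Step 2, so there is no sign that choosing the covariance by AIC adds harm.

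**The case against.** The strongest objection is that the premise is not written down. The article does not say that splines enter the time-by-arm interaction. The AIC sentence directly follows the comparison with generalized least squares, so the options it refers to may be covariance structures only. If splines enter only the common trend, there is no excess. This stands, and it makes the result conditional. It does not remove the point. The model's purpose is to detect different profiles, and a spline confined to the common trend would force the arm difference to be a straight line. If AIC does not settle the splines, no rule does, and the choice is still open once the data are seen.

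Second, 7.2% needs a linear common trend. Under an assumed SD of 9.5 and correlation of 0.6, the contrast T0 − 2 × T4 + T8 has standard error √(6 × 9.5² × 0.4 / 90) = 1.55. A shared HbA1c change of 3 mmol/mol at 6 months, held to 12, then gives z = 3 / 1.55 = 1.9 and an error rate near 6.1%. Such a trend is plausible, because GPs adjust medication in both arms towards a target. This stands, and the figure is therefore an upper value under the Step 2 rule.

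Third, the article values a model that tolerates visits at different times, and a visit factor gives that up. This is a real cost, to be weighed.

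Fourth, spline details commonly belong in an analysis plan, which is not shown. Knots and bases do. But the article itself states a data-driven choice followed by a 5% test, and that conflict is in the text.

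A reader might infer that the trial's main conclusions are at risk. The documents do not support this. The t-tests or Mann-Whitney tests use 12-month values, the powered endpoint is the binary success outcome, and neither uses a spline or AIC.

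**Conclusion.** The concern holds in conditional form. The time shape is left to be settled on the trial data, apparently by AIC, and the chosen model is tested at 5% with no allowance for that choice. For a three-visit outcome the type I error of the interaction test is 7.2% to 7.5% if splines enter the interaction and the common trend is linear. Under joint selection it falls towards 5% as common curvature grows, and it is 5.0% if splines enter only the common trend. The supportable range is 5.0% to 7.5%, under normality, complete data and common visit times. Dosage, which may be discrete or zero, fits these assumptions less well than HbA1c.

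A reader might infer that the protocol makes AIC choose the shape of the arm effect and that the profile tests run at a flat 7%. The text establishes neither. It also gives no number of spline terms, so no figure can be attached to outcomes measured at every visit. The excess is moderate, avoidable and confined to the profile tests.

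**What to change.** For outcomes planned at T0, T4 and T8, fix the mean model in advance: visit as a three-level factor with arm-by-visit terms, adjusted for gender and weight stratum. Test the arm-by-visit terms on 2 df and report the 12-month contrast with its 95% CI. Three levels capture every possible mean profile, so no shape is left to choose and the test holds 5%. AIC may still choose the covariance structure, or unstructured can be fixed in advance.

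For outcomes measured at all visits, state one time shape in advance, and label any spline chosen on the data as descriptive.

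The cost is a few sentences and no new data. One degree of freedom is lost if the true effect is exactly linear, and planned visit replaces actual visit timing.
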